### Interim analyses {21b}

No interim analysis will be performed, and no formal stopping rules are planned. This decision reflects the low anticipated risk of CBT-CP and the modest sample size. Any deviations from this policy, if needed, will be prespecified in the SAP.

### Methods for additional analyses (e.g., subgroup analyses) {20b}

Preplanned subgroup analyses are not powered and will therefore be exploratory only. If conducted, they will examine effect modification by prespecified baseline factors such as age group and pain site. Interaction terms may be added to the LMM, and sensitivity analyses for subgroup or secondary outcome models may also be considered. These additional analyses will be exploratory and interpreted cautiously, with all statistical details, including handling of multiple comparisons, prespecified in the SAP.

### Methods in analysis to handle protocol non-adherence and any statistical methods to handle missing data {20c}

The primary analysis will follow the ITT principle. Protocol non-adherence will not lead to exclusion from the ITT set; per-protocol analyses are not planned. Missing outcome data will be handled within the LMM framework, and no special imputation is applied for the primary analysis. As sensitivity analyses, best-case and worst-case scenarios will be examined using hypothetical values defined a priori and prespecified in the SAP.

### Plans to give access to the full protocol, participant-level data, and statistical code {31c}

The protocol is publicly available through the University Hospital Medical Information Network Clinical Trials Registry (UMIN000042798). This article provides the full protocol with additional methodological details beyond what is available in the registry. In line with open science practices, the finalized SAP will also be made publicly available through the same registry before database lock.

After publication of the main results, de-identified participant-level data, the associated data dictionary, and statistical code will be made available upon reasonable request to the corresponding author, following approval by the relevant ethics committee. Intervention materials, including the CBT-CP workbook and therapist manual, are planned to be published after study completion to support dissemination in Japan.

## Oversight and monitoring

### Composition of the coordinating center and trial steering committee {5d}

The coordinating center for this trial is located at Kansai University, led by the principal investigator, who is responsible for overall trial management and day-to-day coordination. Although no independent trial office is established, the principal investigator directly oversees all organizational aspects of the study. In addition, a research assistant at the National Center of Neurology and Psychiatry assists with tasks related to the EDC system and data coordination.

Oversight of the trial is provided through a Trial Steering Committee convened every 2 months. Attendance is prioritized to ensure that the principal investigator and the site principal investigators (or, when necessary, a delegate from each site such as a therapist) are present. However, all trial team members are invited to participate, and attendance by additional investigators or therapists beyond the site principal investigators is welcomed. The committee reviews recruitment progress, enrollment numbers, reasons for discontinuation or dropout, adverse events, and data entry status, and also serves as the forum for discussing and, when necessary, adjudicating issues such as the interpretation of inclusion/exclusion criteria, given the heterogeneous clinical profiles of patients with chronic pain.

Day-to-day project management is conducted by the principal investigator at Kansai University, with technical support for the EDC system provided by the Translational Medical Center of the National Center of Neurology and Psychiatry. At each study site, the site principal investigator (a collaborating physician) holds ultimate responsibility for local trial conduct, including patient recruitment, informed consent, and adherence to protocol procedures.

No separate stakeholder or public involvement group has been established for this trial.

### Composition of the data monitoring committee, its role and reporting structure {21a}

No independent data monitoring committee has been established for this trial because the intervention (CBT-CP) is a non-invasive psychological therapy. Although some questionnaires include sensitive items such as suicidal ideation and self-injurious behavior, the trial is classified as involving only minor invasions, and according to ethical and regulatory standards in Japan, a formal committee of this kind is not required.

Instead, oversight of safety and trial conduct is ensured through the structures described in Item 5d. In brief, a Trial Steering Committee meets every 2 months to review recruitment, dropouts, adverse events, and data entry. Serious adverse events are immediately shared with all trial team members via a mailing list, and appropriate action is coordinated. In addition, the principal investigator and a data coordinator monitor the electronic data capture system for missing data or deviations, while each site principal investigator checks document retention, data accuracy, and consent procedures, initiating additional monitoring as needed in accordance with institutional regulations.

### Adverse event reporting and harms {22}

Although CBT-CP is classified as involving only minor invasions and no serious adverse events attributable to the intervention are anticipated, adverse events will be systematically monitored at every visit. At each visit, physicians, therapists, or a research assistant will verbally check for any adverse events, and participants may also report events spontaneously at any time.

All adverse events and serious adverse events will be recorded and reviewed from a clinical perspective, including considerations of their seriousness and potential relationship to the intervention. These judgments will be made jointly by the principal investigator and the site principal investigator, with precedence given to the clinical judgment of the site. Any serious adverse event will be promptly reported to the head of the institution and to the institutional ethics committee, as required by institutional and national regulations, and will also be shared with all trial team members to coordinate an appropriate response. An ad hoc meeting may be convened if necessary to determine implications for the trial.

At the site level, each site principal investigator is responsible for ensuring that source documents are retained and that reporting procedures are properly implemented. Clinical significance will always be prioritized in deciding whether an individual participant continues treatment, with decisions made in consultation with the site principal investigator and the attending physician.

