### Trial design {8}

The study uses a multicenter, open-label, randomized, parallel-group superiority design and will involve 60 patients aged 20–80 years with chronic pain. Initial evaluation is conducted after obtaining informed consent, and eligible patients undergo a baseline assessment within 4 weeks and are enrolled as participants. Participants are randomized in a 1:1 allocation ratio to the intervention group (TAU plus an eight-session CBT-CP program) or the waitlist control group (TAU only). Participants in the waitlist group continue their usual care without CBT-CP until the post-assessment at 15 ± 2 weeks after randomization, after which they are offered the intervention.

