### Intervention description {11a}

CBT-CP in this study is a structured and manualized eight-session program, with an original workbook and worksheet consisting of psycho-education, relaxation training, activity pacing, cognitive restructuring, and summary and relapse prevention (Table 1). Materials from the pilot version of the program have already been made freely available to healthcare professionals via the study website (in Japanese), and the present trial materials are planned to be published after study completion to support dissemination of CBT-CP in Japan. Participants will undergo eight sessions of CBT-CP, each lasting approximately 40 min, with the aim of completing the program within 14 weeks. If necessary, sessions may extend beyond the 15th week; however, the post-assessment is conducted at 15 ± 2 weeks irrespective of the intervention schedule. Homework will be provided in each session so that participants can practice the skills learned in real-life situations. The sessions are arranged face-to-face and weekly, unless inconvenient for the participant or therapist. If the therapist and participant cannot complete all the content in eight sessions and both deem it necessary, up to two additional sessions may be permitted.

**Table 1 Tab1:** Outline of the CBT-CP program

Session	Components	Homework
1	Psycho-education regarding CBT and chronic pain (CBT model, self-monitoring) and goal setting	Identifying vicious cycles using the CBT model
2	Relaxation training (breathing method, progressive muscle relaxation)	Practicing relaxation
3	Activity pacing 1 (reviewing the relationship between behavior and pain)	Recording activity log
4	Activity pacing 2 (setting the pace of activity and rest periods)	Practicing the set activity
5	Activity pacing 3 (adjusting the pace, including countermeasures against obstacles to activity)	Practicing activity including obstacle countermeasures
6	Cognitive restructuring 1 (identifying and distancing cognitive factors that interfere with activity)	Identifying obstructive cognition
7	Cognitive restructuring 2 (attempting to alter cognitive factors that interfere with activity)	Distancing from and restructuring the cognition
8	Summary and relapse prevention	Continuing to use the skills that have served them well

*Abbreviations: CBT-CP* cognitive behavioral therapy for chronic pain, *CBT* cognitive behavioral therapy

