### Relevant concomitant care permitted or prohibited during the trial {11d}

To appropriately evaluate the efficacy of the intervention, concomitant care is restricted during the study period. Participants are permitted to continue their stable usual care, such as prescription medications or physical therapy, provided that the type, dosage, and administration remain unchanged. In contrast, they are asked not to (1) initiate other psychotherapy or participate in other clinical trials; or (2) begin medical examinations or treatments that meet the exclusion criteria, such as interventional pain procedures, medical narcotics, or intravenous infusions for pain relief. If a change in usual care is medically necessary, this takes priority, and the participant is instructed to report the change at the next visit. When participants have an attending physician at another hospital, a written summary of the study requirements is also sent to the physician to request that the participant’s usual care remain unchanged from enrollment until the post-assessment.

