#### Process measures

At the start of each visit, physicians, therapists, or a research assistant verbally check for adverse events and any changes in usual care. During the intervention period, at the beginning of each session, participants rate their sense of completeness, average pain intensity, and sense of coping with pain in the last week on an 11-point scale (0–10) by the therapist.

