## Data collection and management

### Plans for assessment and collection of outcomes {18a}

As shown in Table 2, the primary outcome, secondary outcomes and psychosocial variables, demographic and clinical characteristics, and process measures are assessed. Outcomes and psychosocial variables are self-reported using A4 booklet-format questionnaires. Demographic and clinical characteristics at the initial evaluation, as well as process measures during CBT-CP sessions, are obtained verbally by collaborating physicians, therapists, or a research assistant and recorded on standardized forms.

**Table 2 Tab2:** Schematic diagram for the assessment schedule (SPIRIT Fig. 2013)

Time points	Initial evaluation	Baseline assessment	Intervention period	Post-assessment	Follow-up assessment
Visit	1	2	3–10	11	12
Week	−4–0	0	1–14	15 ± 2	27 ± 2
Demographic and clinical characteristics					
Eligibility criteria	V				
Demographic information	V				
Clinical information	V				
Treatment history and status	V				
Primary outcome					
EQ-5D-5L		S		S	S
Secondary outcomes and psychosocial variables					
SF-12		S		S	S
NRS		S		S	S
PDAS		S		S	S
PHQ-9		S		S	S
PCS		S		S	S
TSK-11		S		S	S
PSEQ		S		S	S
STarT Back		S			
SSS-8		S			
Process measures					
Adverse events		V	V	V	V
Changes in usual care		V	V	V	V
Sense of completeness			V		
Average pain intensity			V		
Sense of coping with pain			V		

*Abbreviations and codes*: *S* self-reported by participant, *V* verbally obtained by a physician, therapist, or research assistant, *EQ-5D-5L* EuroQol five-dimensional questionnaire five-level, *SF-12* Medical Outcomes Study 12-Item Short Form Health Survey, *NRS* numerical rating scale, *PDAS* Pain Disability Assessment Scale, *PHQ-9* Patient Health Questionnaire-9, *PCS* Pain Catastrophizing Scale, *TSK-11* Tampa Scale for Kinesiophobia 11, *PSEQ* Pain Self-Efficacy Questionnaire, *STarT Back* Keele STarT Back Screening Tool generic condition, *SSS-8* Somatic Symptom Scale-8

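### Adverse events and usual-care changes are prompted at about 9 contacts after randomisation in the CBT arm but, as described, at one in the waitlist arm, so counts by arm are likely to differ even at equal true rates

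*Protocol article*

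**What the plan says.** The section on adverse event reporting and harms (item 22) states that "adverse events will be systematically monitored at every visit", and adds that participants may report events spontaneously at any time. The Process measures section describes the mechanism: "At the start of each visit, physicians, therapists, or a research assistant verbally check for adverse events and any changes in usual care".

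Table 2, under the plans for assessment and collection of outcomes (item 18a), has the columns "Time points Initial evaluation Baseline assessment Intervention period Post-assessment Follow-up assessment". The two relevant rows read "Adverse events V V V V" and "Changes in usual care V V V V", so both items are obtained verbally at baseline, in the intervention period (visits 3–10, weeks 1–14), at post-assessment (visit 11) and at follow-up (visit 12). The table is not split by arm.

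The intervention description (item 11a) says "Participants will undergo eight sessions of CBT-CP, each lasting approximately 40 min", and allows up to two more. For the comparator, the trial design section (item 8) says "Participants in the waitlist group continue their usual care without CBT-CP until the post-assessment". Item 18a also says that therapists see participants only to deliver CBT-CP. If usual care has to change, item 11d says "the participant is instructed to report the change at the next visit".

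Both arms have the post-assessment at 15 ± 2 weeks. Item 13 lets it be completed by post or telephone when attendance within the window is not possible.

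**The concern.** Prompted collection follows the visit schedule, and between baseline and post-assessment the only trial visits described are CBT sessions. The arms are therefore asked about events with very different frequency over the same calendar period. More frequent asking tends to record more events, so a count by arm mixes true incidence with opportunity to report.

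Three uses of the data are exposed.

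- **Harms.** Any table of adverse events by arm would tend to show more in the CBT arm even if the true rates were equal.
- **Co-intervention.** The comparator is defined as usual care continued without new treatments or changes in type, dosage or administration (item 6b). The check on whether that held is sparsest in the arm that consists of usual care alone. The spontaneous-report provision is written for adverse events, not for usual-care changes.
- **Oversight.** The steering committee reviews adverse events every 2 months in place of a data monitoring committee (item 21a). Before the post-assessment, it would see only spontaneous reports from waitlist participants.

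The bias and limitations paragraphs of the article do not mention unequal prompting.

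**Working it through.** **Step 1: count of prompted checks.** Inputs are Table 2 (visit numbers), item 11a (eight sessions, up to two extra) and item 8 (no CBT-CP for the waitlist until post-assessment).

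- Intervention-period visits in Table 2: 10 − 3 + 1 = 8, which matches the eight sessions.
- CBT arm, after randomisation through post-assessment: 8 + 1 = 9. With both optional sessions, if they fall before the post-assessment: 8 + 2 + 1 = 11.
- Waitlist arm over the same period: 1, the post-assessment itself.
- Strictly between baseline and post-assessment: 8 (up to 10) against 0.

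The waitlist figure is an inference. It rests on the absence of any described trial contact in that interval. The article does not say whether a usual-care hospital appointment counts as a visit.

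**Step 2: what unequal prompting could do to the counts.** The document gives no recall or reporting rate, so this step is an illustration under stated assumptions:

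- true event rates are equal in both arms, and events are uniform over T = 15 weeks;
- an event is recorded at the next check with probability exp(−gap/τ), where τ is an assumed recall time constant in weeks;
- spontaneous reports are not modelled.

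For check times that divide the 15 weeks into gaps g, the expected share of events recorded is

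share = (τ/T) × Σ[1 − exp(−g/τ)].

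Waitlist: one gap of 15 weeks. CBT with weekly sessions: eight gaps of 1 week, then one of 7 weeks. CBT with eight sessions spread over weeks 1–14: gaps of 1 week, seven of 13/7 weeks, then 1 week.

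Example at τ = 4:

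- Waitlist: (4/15) × [1 − exp(−15/4)] = 0.26.
- CBT weekly: (4/15) × {8 × [1 − exp(−1/4)] + [1 − exp(−7/4)]} = 0.69.
- Ratio before rounding: 2.66.

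| τ (weeks) | Waitlist share | CBT share, weekly / spread | Ratio CBT:waitlist, weekly / spread |
|---|---|---|---|
| 2 | 0.13 | 0.55 / 0.67 | 4.1 / 5.0 |
| 4 | 0.26 | 0.69 / 0.81 | 2.7 / 3.1 |
| 8 | 0.45 | 0.81 / 0.90 | 1.8 / 2.0 |
| 26 | 0.76 | 0.93 / 0.97 | 1.2 / 1.3 |
| perfect recall | 1.00 | 1.00 / 1.00 | 1.0 / 1.0 |

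Within this model the ratio exceeds 1 for every finite τ, so the direction does not depend on the value chosen. The size does. Spontaneous reports made at the same rate in both arms would pull every ratio towards 1.

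**Step 3: mailed assessments.** Table 2 codes both items as verbally obtained, while the self-completed booklet carries the outcomes and psychosocial variables. The article does not describe how the verbal check is made when the post-assessment is returned by post. For such a waitlist participant even the single prompt is uncertain.

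**The case against.** The strongest reply has five parts.

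1. **Spontaneous reporting is open to both arms at any time.** This stands. It softens the imbalance for adverse events but does not equalise the prompting.
2. **No between-arm test of adverse events is stated.** This stands too. Item 22 uses events for clinical review of seriousness and relationship to the intervention, and harms tabulation may be left to the analysis plan. The collection schedule, however, is fixed in the protocol, and analysis cannot recover events that were never elicited.
3. **The waitlist count is inferred.** Physicians are among those who check at visits, and many participants come from the participating hospitals' own clinics. Some waitlist participants may be asked at routine appointments. The article neither says so nor schedules it.
4. **Recall may be good.** Serious events are unlikely to be forgotten, and a new drug or procedure often persists or is documented. The single waitlist check can also cover the whole period retrospectively.
5. **Unequal contact is common to therapy-versus-waitlist designs.** True, but that does not prevent naming one comparable source for both arms.

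A reader might go further and infer that counts by arm are bound to differ, or that nine times the checks means something like nine times the events. The document supports neither. With complete recall at week 15 the ratio is 1.0, and the number of checks does not translate directly into a number of events.

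**Conclusion.** The point holds as a weakness in comparability. Prompted checks after randomisation run at about 9 (up to 11) in the CBT arm against 1 in the waitlist arm, as far as the article describes. Recorded adverse events and usual-care changes are therefore likely to be higher in the CBT arm at equal true rates.

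The count rests on reading visits 3–10 as the CBT sessions and on no other waitlist contact being described. The size rests wholly on an assumed recall model, with a ratio from 1.0 to about 5, and should not be quoted as an estimate for this trial.

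A reader might also infer that the trial's main result is compromised. It is not: EQ-5D-5L is collected at the same assessments in both arms, so the primary analysis is not affected. What is affected is the interpretation of harms and of usual-care stability by arm.

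**What to change.** - At the post-assessment, ask both arms the same structured question on adverse events and usual-care changes, covering the whole period since randomisation. Include it in mailed and telephone completions.
- Use that source for any presentation by arm.
- List events reported at CBT sessions separately, and do not compare them with the waitlist arm.
- State in the report that prompting was unequal, and that the common question reduces the imbalance without fully removing it.

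The cost is one item on a form for an assessment already scheduled in both arms, plus one reporting rule. There are two downsides. Recall over about 15 weeks will miss minor events. Participants asked at earlier sessions may also remember more at week 15, so the misses cannot be assumed equal in the two arms.

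As of September 2025, 40 of 60 participants were enrolled and recruitment was extended to March 2027. The new item can therefore still cover those yet to reach post-assessment. For the others, the reporting rule can be applied where the record shows the visit at which an event was elicited.

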### Frequency and plans for auditing trial conduct {23}

Because this study involves only a psychological intervention classified as involving minor invasions, and because in Japan such trials are in principle not required to undergo monitoring or auditing, no independent audit of trial conduct is planned. Instead, oversight is maintained through meetings of all trial team members held every 2 months, during which trial progress and safety issues (e.g., recruitment, discontinuations, and adverse events) are reviewed, and through ongoing monitoring of data entry within the EDC system. Each site principal investigator also checks source documents and consent procedures in accordance with institutional regulations, and institutional ethics committees review trial conduct as required.

### Plans for communicating important protocol amendments to relevant parties (e.g., trial participants, ethical committees) {25}

Any important protocol amendments will be reviewed and approved by the institutional ethics committees before implementation, updated in the trial registry, and communicated to all trial team members. When amendments may affect participants’ willingness to continue, updated information will be provided and re-consent will be obtained as required.

